## Abstract

**Background:**

Chronic thromboembolic pulmonary hypertension (CTEPH) is a progressive pulmonary vascular disorder with substantial morbidity and mortality, also a disease underdiagnosed and undertreated. It is potentially curable by pulmonary endarterectomy (PEA) in patients with surgically accessible thrombi. Balloon pulmonary angioplasty (BPA) and targeted medical therapy are options for patients with distal lesions or persistent/recurrent pulmonary hypertension after PEA. There is an urgent need to increase the awareness of CTEPH. Qualified CTEPH centers are still quite limited. Baseline characteristics, management pattern and clinical outcome of CTEPH in China needs to be reported.

**Methods and design:**

The CHinese reAl-world study to iNvestigate the manaGEment pattern and outcomes of chronic thromboembolic pulmonary hypertension (CHANGE) study is designed to provide the multimodality treatment pattern and clinical outcomes of CTEPH in China. Consecutive patients who are ≥ 14 year-old and diagnosed with CTEPH are enrolled. The diagnosis of CTEPH is confirmed in right heart catheterization and imaging examinations. The multimodality therapeutic strategy, which consists of PEA, BPA and targeted medical therapy, is made by a multidisciplinary team. The blood sample and tissue from PEA are stored in the central biobank for further research. The patients receive regular follow-up every 3 or 6 months for at least 3 years. The primary outcomes include all-cause mortality and changes in functional and hemodynamic parameters from baseline. The secondary outcomes include the proportion of patients experiencing lung transplantation, the proportion of patients experiencing heart and lung transplantation, and changes in health-related quality of life. Up to 31 December 2023, the study has enrolled 1500 eligible patients from 18 expert centers.

**Conclusions:**

As a real-world study, the CHANGE study is expected to increase our understanding of CTEPH, and to fill the gap between guidelines and the clinical practice in the diagnosis, assessment and treatment of patients with CTEPH.

**Registration Number in ClinicalTrials.gov:**

NCT05311072.

## Introduction

Chronic thromboembolic pulmonary hypertension (CTEPH) which classified as group 4 pulmonary hypertension (PH) in the European Society of Cardiology (ESC)/European Respiratory Society (ERS) 2022 guidelines, is a disease caused by the persistent stenosis or obliteration of pulmonary arteries by organized intraluminal thrombi and consequent pulmonary vessel remodeling [1]. The exact incidence of CTEPH after acute PE remains unknown, however, some studies reported it ranges between 0.4% and 6.2% [2]. In the USA and Europe, the crude annual incidence of crude annual full (i.e. diagnosed and undiagnosed) incidence of CTEPH were 3–5 cases per 100,000 population, while in Japan the rate was lower at 1.9 per 100,000 population [3].

Till today, CTEPH is still a disease underdiagnosed and undertreated. Only 7-29% of CTEPH cases in Europe and the United States were diagnosed in 2013, and the majority of patients were in the late stage of disease at diagnosis, with New York Heart Association functional class III/IV [3]. Therefore, there is an urgent need to increase the awareness of CTEPH. In addition, the risk assessment strategy for patients with CTEPH, especially for the patients with inoperable disease, need to be identified in registry-based studies [4].

Great progress has been made these years in the therapeutic strategy of CTEPH. CTEPH is potentially curable by pulmonary endarterectomy (PEA) in patients with surgically accessible thrombi in the main, lobar or segmental pulmonary arteries [5]. However, PEA is not feasible in all patients; up to a half of the patients are considered inoperable and up to 51% develop persistent/recurrent PH after undergoing PEA [6–9]. Balloon pulmonary angioplasty (BPA) is an option for CTEPH patients with lesions in the distal pulmonary arteries. The specific medication for pulmonary arterial hypertension (PAH) can also be used in patients with CTEPH, since they have similar pulmonary vessel remodeling. Due to the progress in the surgical and interventional therapy technic as well as the development of PAH specific therapy, the prognosis and life quality of patients with CTEPH have been improved. There is still a gap between the normalized management and real-world clinical practice. Moreover, qualified CTEPH centers, in which PEA and BPA can be performed with satisfactory quantity and quality, are quite limited in China. The existing studies on CTEPH have the limitations with long time-span and relative small sample size, in which limited patients received BPA or novel target therapy. Thus, they could not accurately reflect the current status in the new era of multimodality therapy in CTEPH.

In a large international CTEPH registry with 679 patients, the 3-year survival was 89% in operated patients and 70% in non-operated patients, respectively [10]. The 5-year and 10-year survival was 82 and 75%, respectively, reported by the University of California, San Diego in the United States, known as the most experienced center in PEA [11]. The therapeutic effect and long-term outcome of patients with CTEPH need to be identified in a large cohort in Asia. High-quality studies in the real world are required to further increase the understanding of CTEPH, including the clinical characteristics, management pattern, outcomes of CTEPH and related risk factors.

## Methods

### Study objective and design

The CHinese reAl-world study to iNvestigate the manaGEment pattern and outcomes of chronic thromboembolic pulmonary hypertension (CHANGE) study aims to investigate the demographic and clinical characteristics, the management pattern, the outcomes of CTEPH and related risk factors. It’s a multicenter, prospective observational study, which enrolls and follows up newly-diagnosed CTEPH patients in a longitudinal setting. Their baseline information, therapeutic pattern and prognosis were collected. Design and flowchart of the study are presented in Fig. 1. The patients enrolled are followed up for at least 3 years with every 3 or 6 months.

**Fig. 1 Fig1:**
[figure not shown]
Design and flowchart of the study CTEPH: chronic thromboembolic pulmonary hypertension; VTE: venous thromboembolism; CTEPD: chronic thromboembolic pulmonary disease; VQ: ventilation/perfusion; CTPA: computer tomography pulmonary angiography; MRPA: magnetic resonance pulmonary angiography; PA: pulmonary angiograph; RHC, right heart catheterization; mPAP: mean pulmonary arterial pressure; PAWP: pulmonary artery wedge pressure; PVR: pulmonary vascular resistance; WHO-FC: WHO functional class; 6MWD: 6-minute walking distance; CMR: cardiac magnetic resonance; CPET: cardiopulmonary exercise testing; MDT: multidisciplinary team; PEA: pulmonary endarterectomy; BPA: balloon pulmonary angioplasty; PAH: pulmonary arterial hypertension

### Study hospitals and patient enrollment

In the CHANGE-CTEPH study, there are 18 centers settings from 9 provincial administrative regions in mainland China. All of tertiary and teaching hospitals with rich experience in the management of abundant patients with PH. Most of the participating centres were referral centres for PEA and/or BPA.

Consecutive patients who are ≥ 14 year-old, diagnosed with CTEPH and willing to sign the informed consent are enrolled. The diagnosis of CTEPH needs to meet the following criteria: (1) mismatched perfusion defects on ventilation/perfusion (VQ) scintigraphy and specific diagnostic signs for CTEPH seen by conventional pulmonary angiography (PA), computer tomography pulmonary angiography (CTPA), or magnetic resonance pulmonary angiography (MRPA) such as ring-like stenosis, webs/slits and chronic total occlusions (pouch lesions or tapered lesions), with effective anticoagulation for at least 3 months; (2) precapillary PH proved by right heart catheterization (RHC), defined as mean pulmonary artery pressure (mPAP) ≥ 20mmHg with pulmonary artery wedge pressure (PAWP) ≤ 15 mmHg and pulmonary vascular resistance (PVR) > 2 Wood’s Units.

The exclusion criteria: (1) diagnosed with other diseases in group 4 PH, like systemic vasculitis without connective tissue disease and pulmonary tumors; (2) informed consent are not available; (3) not able to complete the follow-up.

### Baseline assessment

All the patients enrolled receive imaging examinations (including VQ scan, CTPA, MRPA or PA) and RHC at baseline, in order to confirm the diagnosis of CTEPH. The baseline information is collected, including the demographics, symptoms and signs, past medical history, laboratory findings (complete blood cell count, coagulation test, liver and renal function, brain natriuretic peptide (BNP)/N terminal-proBNP (NT-proBNP), thrombophilia test et al.), electrocardiogram, ultrasonic cardiogram, imaging examinations and RHC data. The WHO-functional classification (WHO-FC), 6-minute walking distance (6MWD) and initial therapy (including medication, surgery and interventional therapy) are also recorded.

### Biospecimen and biobank

Blood samples of enrolled eligible patients who are able to provide written consent are collected via local well-trained investigators according to critical standard operating procedure. The biospecimen will be centrifuged, divided into aliquots (plasma, serum, or blood cells, respectively) as each participating center and transported with dry ice to the central biobank, which was established within China-Japan Friendship Hospital, and then stored at − 80 °C for further genetic and molecular analyses.

The tissue from PEA of enrolled eligible patients who received PEA is also stored in the central biobank in China-Japan Friendship Hospital after the histopathological observation. Human pulmonary arterial endothelial cells and smooth muscle cells are isolated, cultured and cryopreserved for further research.

### Therapeutic strategy

All the patients received a life-long anticoagulation, with warfarin, direct oral anticoagulants （DOACs） or low-molecular-weight heparin. The therapeutic strategy is made by a multidisciplinary team (MDT) consist of PH specialist, PEA surgeon, interventionist, radiologist experienced in thoracic imaging, anesthesiologist and intensive care specialist. The patients with surgically accessible thrombi in the main, lobar or segmental pulmonary arteries and who are willing to receive surgery will receive PEA. The patients who are considered inoperable in the first center will go for consultation in another PH center. BPA and PAH target medication are used in patients who are inoperable or unwilling to receive surgery, and who have recurrent PH after PEA, based on the experience of pulmonologist, cardiologist, and interventional radiologist in each center. Diuretics and cardiotonics are selectively used in the patients with right heart dysfunction. Patients whose cardiopulmonary function is stable also receive rehabilitation during hospitalization and at home.

### Follow-up and endpoints

The patients receive regular follow-up every 3 or 6 months after enrollment for at least three years. For each follow-up, they receive inquiry, physical examination, 6-minute walking test (6MWT), blood tests, electrocardiogram, ultrasonic cardiogram, VQ scan or CTPA and RHC. Cardiopulmonary exercise testing (CPET) and cardiac MR are arranged in selected patients. The therapeutic strategy is modified according to the assessment of each follow-up. If the patients are admitted to the hospital unexpectedly, the cause of hospitalization, the change of symptoms and treatment since last visit, 6MWD, WHO-FC and the change of PVR will be recorded.

The primary outcomes include all-cause mortality and changes in functional and hemodynamic parameters from baseline. The secondary outcomes include the proportion of patients experiencing lung transplantation, the proportion of patients experiencing heart and lung transplantation, and changes in health-related quality of life. The study outcomes were listed in Table 1.

**Table 1 Tab1:** Primary, secondary, and safety outcomes

Outcomes	Main indicators
**Primary outcomes**	
all-cause mortality	
the change of functional parameters from baseline	functional parameters include 6MWD, WHO-FC and BNP/NT-proBNP
the change of hemodynamic parameters from baseline	hemodynamic parameters include mPAP, PVR, CO and CI
**Secondary outcomes**	
lung or heart and lung transplantation	proportion of patients experiencing lung or heart and lung transplantation due to severe right heart failure during the study
changes of health related quality of life	change of quality of life measured with the EQ-5D-5L or EmPHasis-10

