## Discussion

The CHANGE study is designed to provide data on the management pattern and outcomes of CTEPH in China, as well as to reveal the intrinsic etiology and pathogenesis of the disease. It is a national prospective multicenter ongoing registry on the diagnosis, initial treatment, long-time management and prognosis of CTEPH. It was launched since 2016 in China, and until 31 December 2023 it has enrolled 1500 potentially eligible patients.

Up-to-date, the study has the largest sample size set in the real-world in China and continues to consecutively recruit eligible patients, which offers efficient statistical power in data analyses and robust conclusion interpretation. As of December 2024, the enrolled CTEPH patients in the CHANGE registry have received regular follow-ups every three or six months for at least 3 years, which provides opportunities to investigate the long-term sequelae of CTEPH.

Since two decades ago, registry studies on CTEPH have been conducted all over the world, predominantly distributed in Europe and the United States. There are also CTEPH registries in Asian countries including China. Several representative ongoing large registries on CTEPH are summarized in Table 2. The majority of these registries launched before 2010, when the surgical and interventional therapeutic technique was still immature and the application of PAH-specific drugs were quite limited.

**Table 2 Tab2:** Preexisting registry studies on CTEPH

	Inclusion criteria	Number of CTEPH patients	Number of PEA patients	Enrolling time
International CTEPH Association (ICA) [12]	newly diagnosed patients fulfilling the following criteria: (1) be willing to provide informed consent, (2) have been treated with anticoagulation for at least 3 months before diagnosis of CTEPH established at the RHC with mPAP ⩾25mmHg at rest, abnormal ventilation/perfusion scan, pulmonary angiogram, CTPA or MRPA confirming chronic thromboembolic obstructions	1010	649	February 2015- September 2016
United States [17]	patients newly diagnosed (< 6 months) with CTEPH (mPAP ≥ 25mmHg in RHC and radiologic confirmation of CTEPH)	750	566	2015–2018
Europe and Canada [18]	newly diagnosed (≤ 6 months) consecutive patients with CTEPH (mPAP ≥ 25mmHg in RHC at rest or ≥ 30 mmHg after exercise and a PAWP ≤ 15 mmHg) who did not receive PAH-targeted treatment before diagnosis	679	386	February 2007- January 2009

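### The transplant secondary outcome is stated inconsistently: separate proportions with no cause restriction in the Abstract and endpoint text, but one combined proportion limited to severe right heart failure in Table 1, and as a raw proportion over unequal follow-up

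*Protocol article*

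**What the plan says.** The article defines the transplant outcome in three places.

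- **Abstract, methods and design:** "The secondary outcomes include the proportion of patients experiencing lung transplantation, the proportion of patients experiencing heart and lung transplantation". No cause is named.
- **Methods, follow-up and endpoints:** the same pair, "the proportion of patients experiencing lung transplantation, the proportion of patients experiencing heart and lung transplantation", again with no cause. The paragraph closes with "The study outcomes were listed in Table 1", so the table is offered as a statement of the same outcomes.
- **Table 1, secondary outcomes:** one row covering both operations, whose indicator is the "proportion of patients experiencing lung or heart and lung transplantation due to severe right heart failure during the study".

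On observation time, the section on study objective and design says "The patients enrolled are followed up for at least 3 years with every 3 or 6 months". The Discussion says that the registry was launched in 2016 and that "until 31 December 2023 it has enrolled 1500 potentially eligible patients".

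**The concern.** The text and the table differ in two ways. The text has two proportions and the table has one. The text places no limit on the reason for transplantation, while the table counts only operations attributed to severe right heart failure.

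The second difference is the one that matters, because it acts on the numerator. A patient transplanted for another stated reason is an event under the text and a non-event under Table 1. The article does not say which version governs. With two published definitions, the one to report could be chosen after the data are seen.

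A further weakness lies in the form of the measure. A simple proportion over the whole study gives a patient enrolled in 2016 and one enrolled in late 2023 the same weight, although their time at risk may differ by years.

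**Working it through.** The article states no transplant rate, sample size or power for this outcome, so there is no figure to reproduce. The check is a comparison of definitions, followed by an illustration on assumed counts.

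**1. Definitions side by side**

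| Feature | Abstract and endpoint text | Table 1 |
|---|---|---|
| Number of proportions | Two | One |
| Operations | Lung; heart and lung, separately | Lung or heart and lung, combined |
| Cause restriction | None stated | Severe right heart failure |
| Time window | None stated | During the study |

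**2. Can one version be derived from the other?** Let L and H be the numbers of patients with each operation, with no patient having both. Let N be the denominator and p the share of transplants attributed to severe right heart failure.

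- Text: L/N and H/N.
- Table 1: p × (L + H)/N.
- Relative shortfall of Table 1 against the sum of the two text figures: 1 − p.

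If p = 1, the Table 1 figure is the sum of the two text figures and the versions agree. If p < 1, it cannot be obtained from them.

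**3. Illustration.** Assumptions: N = 1500 (the enrolment figure, used only as a convenient denominator), and transplant counts of 15 or 30 chosen for the example.

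| Assumed transplants | Text: L/N and H/N | Table 1, p = 60% | p = 80% | p = 100% |
|---|---|---|---|---|
| 15 (10 lung, 5 heart and lung) | 0.67% and 0.33% | 9/1500 = 0.60% | 12/1500 = 0.80% | 15/1500 = 1.00% |
| 30 (20 lung, 10 heart and lung) | 1.33% and 0.67% | 18/1500 = 1.20% | 24/1500 = 1.60% | 30/1500 = 2.00% |

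The relative shortfall is 40%, 20% and 0% in both rows, because it depends only on p. The absolute difference is 0 to 0.4 percentage points with 15 transplants and 0 to 0.8 with 30.

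**4. Unequal follow-up.** A patient enrolled at the end of 2023 completes three years at the end of 2026. A patient enrolled at the end of 2016 and still followed then has ten years. At a constant transplant rate, and ignoring death, expected events per patient scale with time at risk, so the second patient contributes about 10/3 = 3.3 times as much expected risk as the first. This is an upper illustration: death, loss to follow-up, or stopping at three years would shrink the ratio.

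**The case against.** The strongest reply is that the text is a summary and Table 1 supplies the detail. The text names functional and hemodynamic parameters and quality of life only in general terms, and the table adds the variables and instruments. On that reading, the right-heart-failure phrase specifies an outcome that the text merely names, and the single row is a compact way to list both operations.

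This carries weight for the combined row: the combined figure can be built from its parts, so that difference alone would be minor. It does not dispose of the cause restriction. Listing instruments fills in an unspecified term, whereas restricting the cause removes patients from an outcome that the text already states in full.

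Several stronger readings are tempting but not supported:

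- A reader might infer that the text defines an any-cause outcome. It does not use that term, although the article does write all-cause for mortality. The text simply states no restriction.
- A reader might infer that attribution would be an unblinded site judgement. The article makes the investigators who enter data responsible for its accuracy, but does not say who attributes the cause of a transplant. That detail may sit in the full protocol.
- A reader might say that Table 1 undercounts. That presumes the unrestricted version is the intended one, which is the open question.
- The 20% shortfall in the middle of the illustration is not an estimate. The article mentions no transplant for any other reason, so the two versions might select the same patients.

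On follow-up, it can be said that every patient is to be observed for at least three years and that Kaplan-Meier and Cox methods are planned for time-to-event outcomes. Both are true, but a three-year minimum does not equalise time at risk, and the article labels this outcome a proportion. If it were analysed by Kaplan-Meier with deaths censored, the probability of transplantation would be overstated.

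**Conclusion.** The inconsistency is real and can be verified from the article alone. The cause restriction in Table 1 can change which patients count as events, and no passage says which version applies. The size is unknown: the relative difference equals the share of transplants not attributed to severe right heart failure, and the article gives neither that share nor a transplant rate. The illustrated range of 0% to 40% rests entirely on assumed shares of 100% down to 60%.

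The raw proportion is a second, smaller weakness, because enrolment from 2016 to at least the end of 2023 makes follow-up unequal.

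The consequence is limited. This is a secondary outcome in an observational registry, and no stated sample size, power or significance level depends on it. It is a low-priority correction that is cheap to make.

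**What to change.** Use one definition in the Abstract, the endpoint text and Table 1. The preferred form counts all lung or heart and lung transplants as one composite, shows the two components separately, and records the reason for each transplant descriptively. If the restriction to severe right heart failure is intended, state it in all three places.

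Report the outcome as cumulative incidence at 3 years from enrolment, with death as a competing event, in place of a raw proportion over the study. Three years matches the minimum follow-up already planned.

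The cost is a line or two of wording and a minor extra analysis. Follow-up for death and transplantation is already part of the registry; the date of each event, and the reason for transplant if not already captured, must be available. Transplant-free survival could be added, but it is optional and not needed to remove the inconsistency.

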**Safety outcomes**	
bleeding	fatal bleeding, major bleeding, clinically relevant non-major bleeding, based on the ISTH definition [15, 16]
symptomatic recurrence of DVT or PE	reappearance of clinical manifestations or symptoms associated with DVT or PE after a previous episode or treatment, include leg pain, swelling, warmth, redness, or shortness of breath, etc.
complication of treatment interventions (PEA or BPA)	complications include lung injury, haemoptysis, residual pulmonary hypertension, etc.

6MWD: 6-minute walk distance; WHO-FC: WHO-functional class; BNP: brain natriuretic peptide; NT-proBNP: N terminal-probrain natriuretic peptide; mPAP: mean pulmonary arterial pressure; PVR: pulmonary vascular resistance; CO: cardiac output; CI: cardiac index; EQ-5D-5L: 5-level EQ-5D version; ISTH: international society on thrombosis and haemostasis; DVT: deep venous thrombosis; PE: pulmonary embolism; PEA: pulmonary endarterectomy; BPA: balloon pulmonary angioplasty

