The multimodality treatment has been applied more widely in patients with CTEPH in recent years. Numerous unanswered questions and challenges continue to arise in the new era of multimodal CTEPH treatment. There are several scenarios of the multimodality therapy for CTEPH: (1) some patients with inoperable CTEPH receive sequential or simultaneous treatment with targeted medical therapy and BPA; (2) BPA and/or targeted medical therapy have been applied in patients with persistent or recurrent PH after PEA; (3) patients with operable CTEPH but severe hemodynamic impairment could receive PEA after several sessions of BPA ± targeted medical therapy with reduced surgical risk; (4) combination of PEA and BPA might be performed in selected patients with high-risk hemodynamics with unilateral operable and contralateral inoperable disease. It remains unclear which is the best sequence and interval of the hybrid of therapeutic strategy for selected patients. We will try to find the answer to these questions in the real-world study.

In the CHANGE registry, we will also focus on the medical treatment in patients with CTEPH in recent years, especially PAH-specific drugs and anticoagulants. Up to now, riociguat was the only agent approved for the treatment of CTEPH and used as first choice for all CTEPH patients who need PAH-specific therapy. However, riociguat was not available or not included in health insurance in some areas, that limit its application in clinical practice. In addition, other PAH-specific drugs, such as macitentan and subcutaneous treprostinil, also exhibited promising efficacy in CTEPH. PAH-specific drugs which appeared on the market earlier, like sildenafil, tadalafil, bosentan and ambrisentan, were chosen to treat patients with CTEPH when riociguat was not available or well tolerated. It remains to be illustrated which kind of PAH-specific agent and whether combined PAH-specific therapy bring benefit for patients with CTEPH. All the guidelines on CTEPH recommend life-long anticoagulation for CTEPH patients without contradiction. Nonetheless, the effect and safety of DOACs in CTEPH is still controversial and need to be illustrated in both randomized controlled trials and real-world studies.

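### Recurrent DVT or PE is defined by non-specific symptoms with no objective confirmation, so worsening CTEPH can be counted as recurrence and any anticoagulant comparison on this outcome can be diluted or biased

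*Protocol article*

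**What the plan says.** Table 1 of the protocol article lists "symptomatic recurrence of DVT or PE" as a safety outcome and gives as its indicator the return of signs or symptoms "associated with DVT or PE after a previous episode or treatment, include leg pain, swelling, warmth, redness, or shortness of breath, etc". Nothing in that row asks for imaging, evidence of new thrombus or adjudication.

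The bleeding row just above does rest on a formal standard: "fatal bleeding, major bleeding, clinically relevant non-major bleeding, based on the ISTH definition". The row just below collects complications of PEA and BPA, with lung injury and residual pulmonary hypertension among its examples.

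Four other places bear on the point:

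- Follow-up and endpoints: each visit includes "blood tests, electrocardiogram, ultrasonic cardiogram, VQ scan or CTPA and RHC". These scans are not linked to the recurrence outcome, and no leg-vein imaging is listed.
- Study hospitals and patient enrollment: mismatched perfusion defects are part of the entry criteria.
- Introduction: the cited literature puts persistent or recurrent pulmonary hypertension after PEA at up to 51%.
- Discussion: anticoagulants are named as a focus of the registry, and "the effect and safety of DOACs in CTEPH is still controversial".

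**The concern.** Breathlessness is a leading symptom of the disease under study. Leg swelling is also non-specific here: the Therapeutic strategy section foresees right heart dysfunction treated with diuretics. The rule covers symptoms that come back after treatment. A patient who improves after PEA and becomes breathless again because pulmonary hypertension has returned therefore meets it to the letter, without any new clot. Breathlessness from lung injury after BPA can meet it too, and the same episode can then appear in two safety rows.

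Recurrent DVT or PE is the only thrombotic-event outcome in Table 1. If the registry compares anticoagulants, this outcome would carry the question of protection against clots. An outcome that mixes true recurrences with disease progression overstates the rate and weakens or distorts that comparison.

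**Working it through.** **Is there a figure to reproduce?** No. The article gives no recurrence rate, no false-positive rate, no split between anticoagulants and no power calculation. What follows is an illustration.

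**Inputs from the document.** 1500 patients enrolled (Abstract); two-sided significance level 0.05 (Statistical analysis plan section).

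**Assumed inputs.** True risks p1 = 3% and p2 = 6%; every true recurrence is captured; a fraction f of patients without recurrence has qualifying symptoms, equal in both groups; two groups of 750. A simple risk ratio stands in for the planned hazard ratio.

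**Formulas.**

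- Observed risk: q = p + (1 − p)f
- True share of counted events in the lower-risk group: p1/q1; pooled over equal groups: (p1 + p2)/(q1 + q2)
- Power, n per group, with q̄ the mean of q1 and q2: Φ{[(q2 − q1) − 1.96·√(2q̄(1 − q̄)/n)] / √([q1(1 − q1) + q2(1 − q2)]/n)}

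**Example at f = 10%.** q1 = 0.03 + 0.97 × 0.10 = 0.127; q2 = 0.06 + 0.94 × 0.10 = 0.154; ratio 0.154/0.127 = 1.21.

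| f | q1 | q2 | Risk ratio | True share, lower-risk group | True share, pooled | Power |
|---|---|---|---|---|---|---|
| 0 | 3.0% | 6.0% | 2.00 | 100% | 100% | 80% |
| 5% | 7.85% | 10.7% | 1.36 | 38% | 49% | 48% |
| 10% | 12.7% | 15.4% | 1.21 | 24% | 32% | 32% |
| 20% | 22.4% | 24.8% | 1.11 | 13% | 19% | 19% |
| 30% | 32.1% | 34.2% | 1.07 | 9% | 14% | 14% |

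**Sensitivity to the assumed risks.** At 5% against 10%, power is 96% with f = 0, then 81%, 65%, 42% and 29% at f = 5%, 10%, 20% and 30%. At 2% against 3%, power is only 24% even with f = 0. With a 375:1125 split at 3% against 6%, power falls from 64% (f = 0) to 24% (f = 10%).

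**When do false positives outnumber true events?** When (1 − p)f > p, that is f > p/(1 − p): 3.1% at p = 3%, 4.7% at p = 4.5%, 11.1% at p = 10%.

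**Unequal false positives.** Keep the true risks at 3% and 6%.

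- f = 10% in the lower-risk group and 5% in the other: 12.7% against 0.06 + 0.94 × 0.05 = 10.7%, ratio 0.107/0.127 = 0.84. The direction reverses.
- f = 5% and 20%: 7.85% against 0.06 + 0.94 × 0.20 = 24.8%, ratio 0.248/0.0785 = 3.16. The effect is exaggerated.

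Dilution is therefore assured only when f is the same in both groups.

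**The case against.** The row has limiting words. Symptoms must reappear and must be associated with DVT or PE, so breathlessness that simply persists from baseline is not an event. The column is headed *Main indicators*, and fuller criteria may sit in the eCRF or the full protocol, which are not shown. Both points stand and lower the certainty. They do not remove the problem: the table states a working definition, and symptoms that return after treatment satisfy it.

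A reader might infer three stronger claims that the document does not support.

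- *The outcome mainly counts CTEPH.* This needs a recurrence rate and a false-positive rate, and neither is given. It is plausible at modest values of f, but not shown.
- *The outcome cannot show a difference between anticoagulants.* At an assumed 5% against 10% with f = 5%, power is still 81%. The comparison loses strength; it does not become impossible.
- *Anticoagulant safety as a whole is compromised.* Bleeding has its own ISTH-based row and is unaffected. Table 1 does not tie the recurrence row to an anticoagulant comparison, and the Discussion specifies no contrast or effect size.

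Nor can the Introduction's statement that "the majority of patients were in the late stage of disease at diagnosis, with New York Heart Association functional class III/IV" be used as a description of this cohort. It concerns Europe and the United States, and the article gives no functional-class distribution for its own patients. The 51% after PEA is likewise an upper figure from cited literature.

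**Conclusion.** The concern holds in limited form. As worded, the recurrence outcome accepts non-specific symptoms without objective confirmation, so worsening or recurrent CTEPH, or breathlessness after an intervention, can be counted as recurrent thromboembolism. The table fixes this rule itself; it is not a detail left to another document.

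Any false positives inflate the rate. With equal false positives, a comparison of anticoagulants on this outcome moves towards no difference: under the assumed 3% against 6%, the risk ratio falls from 2.0 to 1.21 at f = 10% and to 1.07 at f = 30%. With unequal false positives, for instance where symptom burden differs between the groups, the bias can go either way. The actual size cannot be stated from the document. As a safety outcome with a repairable definition, it should be corrected before any recurrence rate or anticoagulant comparison is reported.

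**What to change.** **Definition.** Count a recurrence only when new or returning symptoms come with objective evidence of new thromboembolism compared with earlier imaging. For PE, use the VQ scan or CTPA already listed at follow-up. The finding must be new, because perfusion defects are present at entry. For DVT, use venous imaging where it was done in routine care. Assessment without knowledge of the anticoagulant is preferable.

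**Reporting.** Report symptom-only or un-imaged episodes separately as suspected, unconfirmed events, outside the main recurrence rate. Add a sensitivity analysis that includes them. State how an episode that also qualifies as a PEA or BPA complication is counted.

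**Timing.** Apply the rule to new events and re-code past events where imaging reports exist.

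**Cost.** Changes to the table and eCRF wording, and the re-coding work. There will be fewer counted events. DVT that was never imaged may be under-counted, since venous imaging is not on the follow-up list. Because follow-up allows either VQ or CTPA, some comparisons with earlier scans will be across modalities and harder to judge. The sensitivity analysis shows how much the un-imaged episodes matter.
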